## Abstract

**Background::**

Routine screening for nontuberculous mycobacterial (NTM) lung disease is dependent on sputum cultures. This is particularly challenging in the cystic fibrosis (CF) population due to reduced sputum production and low culture sensitivity. Biomarkers of infection that do not rely on sputum may lead to earlier diagnosis, but validation trials require a unique prospective design.

**Purpose::**

The rationale of this trial is to investigate the utility of urine lipoarabinomannan (LAM) as a test to identify people with CF with a new positive NTM culture. We hypothesize that urine LAM is a sensitive, non-invasive screening test with a high negative predictive value to identify individuals with a relatively low risk of having positive NTM sputum culture.

**Study design::**

This is a prospective, single-center, non-randomized observational study in adults with CF, 3 years of negative NTM cultures, and no known history of NTM positive cultures. Patients are followed for two year-long observational periods with the primary endpoint being a positive NTM sputum culture within a year of a positive urine LAM result and a secondary endpoint of a positive NTM sputum culture within 3 years of a positive urine LAM result. Study implementation includes remote consent and sample collection to accommodate changes from the COVID-19 pandemic.

**Conclusions::**

This report describes the study design of an observational study aimed at using a urine biomarker to assist in the diagnosis of NTM lung infection in pwCF. If successful, urine LAM could be used as an adjunct to traditional sputum cultures for routine NTM screening.

## INTRODUCTION

People with cystic fibrosis (pwCF) are a population at risk for developing pulmonary nontuberculous mycobacteria (NTM) infection, and despite recent advances in the field, diagnosis and treatment remains challenging (1–3). Historically, approximately 20% of cystic fibrosis (CF) patients have a positive NTM culture over a 5 year period (4); thus, annual screening for NTM is recommended (3). *M. avium* complex (MAC) and *M. abscessus* (MABSC) are responsible for nearly all NTM infections in pwCF living in the US (5). Both species can cause NTM lung disease, which is associated with significant morbidity and mortality.

The diagnosis of NTM lung disease in pwCF is challenging, as co-infections with bacteria such as *P. aeruginosa* and *S. aureus* are common, and may result in identical symptoms and radiographic findings (6). Frequently, NTM may be detected in a culture, but the infection then resolves without treatment or remains indolent for many years. A retrospective review from the Colorado Adult CF Center showed that the majority of participants with a positive NTM culture had transient (23%) or persistent but clinically indolent NTM infection (38.5%) (7). Currently, sputum culture is the “gold standard” for detecting NTM infection and the assay by which all diagnostic and treatment decisions are made (1). However, limitations of sputum culture include slow growth, high cost, and low sensitivity due to the required decontamination steps (3, 8–11). Also, given advancements in CF care and widespread use of cystic fibrosis transmembrane conductance regulator (CFTR) modulator therapy, pwCF are increasingly unable to routinely expectorate sputum (12) and are presenting less often to clinic or with pulmonary exacerbations (13). This combination of factors highlights the need for sputum-independent markers of NTM infection in this population (14).

Lipoarabinomannan (LAM) is a cell wall lipoglycan found in all mycobacteria species and a biomarker of mycobacterial infection (15, 16). During infection, LAM is released from metabolically active or degrading mycobacterial cells into the circulation with subsequent filtration by the kidneys and passed into the urine (17, 18). LAM is a validated biomarker for active tuberculosis (TB) when antigen detection, rather than antibody measurement, is applied (15, 19–23). These antigen detection assays for TB based on LAM are commercially available both as ELISAs and as a point-of-care test. However, the utility of a commercially available TB-specific LAM antigen was tested in a Danish CF clinic and was determined not to be suitable for diagnosis of NTM due to low concentrations of LAM antigen detected in urine from NTM positive pwCF (24). We reported measurable detection of urine LAM utilizing gas chromatography–mass spectrometry (GC-MS) analysis that corresponded with previous NTM culture history in pwCF (n=44) with well-documented NTM status (25). Urine LAM analysis also reflected treatment response in a pwCF receiving bacteriophage therapy for *M. abscessus* (26).

Herein, we present the design of a prospective, single-center, nonrandomized observational study to investigate the utility of urine LAM as a test to identify pwCF with clinically low suspicion for having a sputum culture positive for NTM. The primary objective of this study is to determine the ability of the urine LAM assay to predict continued negative NTM sputum cultures over a 12-month period. Secondary objectives are to determine the ability of the urine LAM assay to predict a new positive NTM sputum culture within 12 months and establish the time between a positive urine LAM assay and a newly positive NTM sputum culture. We hypothesize that urine LAM is a sensitive, non-invasive screening test to identify NTM infection in individuals with a relatively low risk of having a positive NTM sputum culture.

## METHODS

### Study Design

PAINLESS is a prospective, single-center, nonrandomized observational study. The study is approved by the Biomedical Research Alliance of New York (BRANY) review board (20–08-402–528) and is registered in ClinicalTrials.gov (NCT04579211). We comply with the Declaration of Helsinki and Good Clinical Practice guidelines. Written or electronic informed consent is obtained from all participants with a target enrollment of 100. As subject enrollment began on October 23 2020 and continued during restricted clinic access due to the Covid-19 pandemic, informed consent remains available by utilizing an innovative, electronic consenting platform (ClinOne, Inc). The use of electronic consent eliminates the need to have prolonged in-person contact and decreases the risk of infection from COVID-19 and other viruses/bacteria present in a healthcare setting. An instructional video is available for review prior to participation to further explain the rationale for the study, sample collection procedures, and sample timelines (27). Subjects are provided a urine collection kit to expedite sample drop-off. Subjects who are consented in-person are provided written informed consent and may collect the urine specimen at the time of the visit or at home. Subjects are followed on protocol for a minimum of two year-long observation periods (24±3 months). The trial is currently ongoing. The schedule of events is shown in Figure 1 and an overview of the PAINLESS study design and timeline is shown in Figure 2.

### Study population

Adults (≥18 years old) with a confirmed diagnosis of CF followed at the Colorado Adult CF Center who have a minimum of 3 negative NTM cultures with 3 years of available clinical culture data and at least one negative NTM culture within the year prior to enrollment and no known history of previous NTM positive cultures are eligible for enrollment. There are no criteria related to the use of CFTR modulators or other ongoing therapies unrelated to NTM. It is anticipated that up to 90% of participants will be receiving CFTR modulator therapy for the entire duration of the trial, consistent with current usage within the study population. Complete inclusion and exclusion criteria are shown in Table 1.

#### Subject related data

Demographic information including date of birth, sex, and race are recorded. The diagnosis of CF consistent with the 2017 CFF Guidelines is confirmed (28). Dates and results from all available NTM cultures are recorded. A minimum of 3 NTM cultures over a 3 year prior to enrollment must be available and documented, with at least 1 negative within the year previous to enrollment. Use of CFTR modulators is also recorded. All subjects in the PAINLESS Trial must also be enrolled in the CF Foundation Patient Registry (CFFPR) (29). If needed, data may be extracted from the CFFPR for exploratory analysis and long-term follow-up.

#### Sputum collection and culture analysis

All sputum cultures are collected in the context of clinical care. Expectorated or induced sputum samples are collected during clinic visits and hospitalizations. Sputum samples collected at home may be brought to a clinic appointment or shipped using a sputum collection kit. The sputum collection kits, including instructions for collecting and shipping sputum specimens, are routinely ordered by providers to facilitate sputum culture collection. Samples obtained by bronchoscopy (if available) will also be recorded when collected for clinical indications. Microbiology and mycobiology results are recorded in the subject’s electronic medical record and the CFF Patient Registry. Sputum samples are cultured for NTM as well as typical CF pathogens. NTM cultures are performed at the Advanced Diagnostic Laboratories (ADx) at National Jewish Health, which is a national reference laboratory for mycobacteriology species identification and drug resistance testing (30). Following digestion and decontamination, specimens are inoculated on a LJ Slant, Middlebrook 7H11 Agar/ Mitchison 7H11 Selective Agar biplate(s) and MGIT for up to eight weeks. Suspected NTM growth is confirmed from either liquid and solid culture media using a Ziehl-Neelsen staining. Upon growth detection, genomic DNA is isolated for subsequent PCR amplification. A targeted segment of the DNA-directed RNA polymerase subunit beta (*rpoB*) gene is performed to determine molecular identification.

### Urine collection for LAM analysis

The initial urine sample is obtained at enrollment and marks the start of observational year 1. If the subject is consented remotely, the subject completes the electronic consent process prior to collecting the initial urine sample. The initial urine sample is required within 30 days of a NTM sputum sample collected in the context of clinical care. Following enrollment, additional urine samples are collected at the start of observational year 2 and at the end of study. An additional urine collection may occur in the event a subject is found to have a positive NTM sputum culture between the planned collection dates. The urine sample may be collected in the clinic or at home with a collection kit and brought to clinic. Subjects are asked to provide between 20cc to 50cc of urine per collection. After collection, urine samples centrifuged, aliquoted, and stored at −80°C until analysis.

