#### Primary analysis

The primary analyses will focus on establishing the predictive accuracy of the urine LAM assay compared to both NTM culture results from the day of sampling and aggregated culture results from within a year of the LAM measurement date. As a secondary endpoint, we will focus on how well a positive urine LAM assay predicts a positive NTM culture over a three year period. For the primary endpoints, the classification performance of the LAM assay will be assessed with respect to its ability to predict a positive culture at the time of the test and over the 12-month period prior or following the test. Of primary interest are the test’s sensitivity and specificity, but we will also investigate positive predictive power, negative predictive power, percent-agreement, and Cohen’s Kappa. These values will be computed twice using the binary results of the LAM assay (positive or not-positive) paired with either the binary culture results from the time of the test or with the aggregated results over the study interval (*i.e*. ≧1 positive culture versus no positive cultures). We will also investigate if the continuous abundance of LAM is a useful measure by calculating area under the receiver-operator curve, again using culture from the time of the test or aggregated over the 12-month period. Additionally, the multiple repeated observations for each individual in the two 12-month follow-up periods will allow us to perform a time-to-event analysis associating the LAM assay to culture results. Here, Cox proportional hazards regression models will be utilized with time to first positive NTM culture as the outcome and LAM assay (using both the continuous and binary versions) as the time-varying covariate of interest.

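### The look-back half of the 12-month window in the primary accuracy analysis admits urines taken after a first positive culture; these cannot measure prediction and can distort sensitivity and AUC.

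*Protocol article*

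**What the plan says.** **Window.** The Primary analysis section of the protocol article assesses the assay's ability "to predict a positive culture at the time of the test and over the 12-month period prior or following the test". The same section also describes the reference as "aggregated culture results from within a year of the LAM measurement date", which does not limit the direction. One or more positive cultures in the interval makes the pair a case. The measures of main interest are "sensitivity and specificity, but we will also investigate positive predictive power, negative predictive power, percent-agreement" and kappa, with the first two given priority. The AUC for continuous LAM uses the same pairing.

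**Urines.** The first sample is at enrollment, and "additional urine samples are collected at the start of observational year 2 and at the end of study". The section on urine collection adds, for positives that arise between scheduled collections: "An additional urine collection may occur in the event a subject is found to have a positive NTM sputum culture". Culture-negative subjects have no matching extra sample.

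**Question.** The Introduction's primary objective is to predict continued negative cultures over 12 months. A secondary objective is to "predict a new positive NTM sputum culture within 12 months". Both look forward.

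**Entry.** Study population and Table 1 require three years of negative culture data and no known earlier positive (Table 1: for pathogenic NTM).

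**The concern.** An enrollment urine should have no known pathogenic NTM positive in its preceding 12 months, apart from a linked sputum taken within 30 days that later grows NTM. Any other look-back positive has to be an on-study positive followed by a later urine. The look-back half therefore does little for the stated question except classify post-positive urines as cases.

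A urine taken once the subject is already culture-positive says something about detecting established infection. It says nothing about forecasting a first positive or continued negativity. If LAM is positive more often after first culture positivity than before, mixing the two kinds of urine overstates predictive sensitivity and AUC. With about 13 expected cases, a few such urines can move the estimate noticeably. The Discussion says the results will determine whether a larger multi-center trial is feasible.

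**Working it through.** **The plan's own figure.** The Sample size section expects approximately 13 of 100 subjects to have a new positive culture over two years. The figure rests on local historical data that are not shown, so it cannot be reproduced, and it is taken as given.

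**Which urines the look-back reaches.**
1. Scheduled urines are about a year apart. Per the Figure 1 footnotes, the end-of-study visit is the first clinical visit more than 9 months after the start of Year 2.
2. A first positive in Year 1 therefore normally lies within 12 months before the Year 2 urine, and a first positive in Year 2 normally lies within 12 months before the end-of-study urine.
3. So one post-positive urine per case can arise from the schedule alone, without the optional sample. Missed or late urines reduce that number.

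**Inputs.** Cases: 13 (Sample size section). LAM positivity before first culture positivity, s_pre, and after it, s_post: not given in the document. The values below are assumptions, with one pre-positive urine per case.

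**Formula.** Pooled sensitivity = (13 × s_pre + k × s_post) / (13 + k), where k is the number of post-positive urines. It depends on k/13, so the count of 13 matters for the interval and not for the size of the shift.

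**Results with s_pre = 0.50 and s_post = 0.90.**
- Pre-positive urines only (k = 0): 6.5/13 = 0.50.
- Half the cases give one (k = 6.5): (6.5 + 5.85)/19.5 = 0.63.
- All cases give one (k = 13): (6.5 + 11.7)/26 = 0.70.

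**Range, s_post = 0.90.**

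| s_pre | half the cases | all cases |
|---|---|---|
| 0.40 | 0.57 | 0.65 |
| 0.50 | 0.63 | 0.70 |
| 0.60 | 0.70 | 0.75 |
| 0.70 | 0.77 | 0.80 |
| 0.80 | 0.83 | 0.85 |

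**Other direction.** If s_post = s_pre, the shift is zero. If s_post is 0.20 below s_pre, then 0.50 becomes (6.5 + 3.9)/26 = 0.40.

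**Predictive values (illustrative).** Take 200 subject-years, of which 13 are case intervals and 187 are not, and an assumed specificity of 0.85. This gives 158.95 true negatives and 28.05 false positives. Adding 13 post-positive urines moves PPV from 6.5/34.55 = 0.19 to 18.2/46.25 = 0.39. NPV moves from 158.95/165.45 = 96.1% to 158.95/166.75 = 95.3%. In this model specificity does not change.

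**Precision.** In whole numbers, 7/13 has a 95% Clopper-Pearson interval of 0.25 to 0.81. Adding 12/13 post-positive results gives 19/26, with an interval of 0.52 to 0.88. Part of that narrowing is false, because two urines from one subject are counted as independent.

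**The case against.** The strongest reply is that the article condenses a fuller protocol, and that the rule on which urines count as index tests belongs in an analysis plan that is not shown. This stands for the triggered urine. The text says only that it may be collected, and nowhere places it in the accuracy tables. A reader might infer that case-only samples are planned into the primary analysis, but the document does not say so. The reply does not cover the window, because the look-back is stated outright and catches scheduled urines whether or not an extra one is taken.

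Other points on that side also stand:
- **Cox model.** A reader might suspect reverse causation from LAM values measured after the event. The outcome is time to first positive culture, so subjects leave the risk set then and later values do not enter.
- **Time-of-test table.** Cultures are held for up to eight weeks, so a urine prompted by a positive result is not a same-day pair with the culture that prompted it.
- **Direction.** Upward bias is plausible, since the Introduction reports that LAM corresponded with past culture history. It also reports 23% transient infection and a LAM response to treatment, so the bias could vanish or reverse.
- **Primary objective.** On continued negativity, the effect on NPV in the illustration is small and downward.
- **Larger shifts.** A pooled value near 77% can be computed as (6.5 + 26 × 0.90)/39, but it needs two post-positive urines from every case. The document gives no basis for that.

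**Conclusion.** The point holds as a mismatch between a stated window and the stated objectives. The 12-month look-back admits urines taken at or after an on-study positive, and these cannot measure prediction of a new positive or of continued negative cultures.

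Under the assumed 50% and 90%, sensitivity reads 63% to 70% rather than 50%. The size depends wholly on those unstated rates and on how many cases supply a later urine. The supportable wording is that sensitivity and AUC can be inflated, not that they will be. No size is given for the AUC, because the document has nothing on the distribution of LAM.

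Reversing the window alone would not be enough. The Introduction reports 38.5% persistent but indolent infection at this center, so a post-positive urine may be followed by a repeat positive that counts as predicted although it is not new. The point merits a change before analysis. It does not call the design or the sample collection into question.

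**What to change.** For the 12-month predictive 2x2 tables and ROC:
1. Use a forward-only 12-month window.
2. Include only scheduled urines from subjects with no earlier positive NTM culture, other than the sputum linked to that urine within 30 days. Without this exception, an enrollment urine taken days after a sputum that later grows NTM would be lost. Keep that linked pair for the concurrent (time-of-test) table.
3. Remove a subject's later urines from the predictive set after the first positive.
4. Report triggered and post-positive urines in a separate descriptive table.

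The Cox model needs no change beyond dating the event by sputum collection date rather than result date.

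The cost is a short analysis-set statement, with no change to collection. A few urines leave the primary table and the sensitivity interval is wider (in the illustration, 0.25 to 0.81 instead of 0.52 to 0.88). That wider interval describes what about 13 cases can actually show.

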#### LAM assay methods

All urine samples require a hexane wash (1:1 v/v) to remove exogenous lipids and proteins in order to reduce background and increase the limit of detection. Coded samples are separated by hydrophobic interaction chromatography over Octyl Sepharose (OS)-CL 4B. The 40% & 65% n-propanol in 0.1 M NH_4_OAc eluents off the HIC column are processed for GC/MS analysis as previously described (31, 32). GC/MS analyses are carried out using a Thermo GC-TSQ8000 Evo Triple Quad GC mass spectrometer. Chromatograms with respective peaks are integrated manually (*i.e*. peak areas defined manually and integrated areas generated by software) for the estimation of total D-ara and TBSA content. LAM used for standardization and assay validation in this study is purified from *Mtb* and *M. avium* (Figure 3) (33).

## DATA COLLECTION, MANAGEMENT, and ANALYSIS

Study data are collected and managed using the REDCap electronic data capture tools hosted at National Jewish Health. REDCap (Research Electronic Data Capture) is a secure, web-based software platform designed to support data capture for research studies (34, 35). The handling and analysis of the data is conducted using good computing practices for clinical trials, including routine data validation checks. As part of data analysis, the lead biostatistician on the study monitors for data outliers and performs data validation. If data entry errors are encountered, the study database is updated in accordance with the resolved queries. All changes to the study database are documented in an audit trail. Database lock will occur once quality assurance procedures have been completed and will be maintained for 5 years.

### General analysis plan

#### Sample size

Planned sample size is 100 subjects. Based on historical data from the Colorado Adult CF Program, we anticipate approximately 13 subjects will be identified with a new positive NTM culture over the course of two year-long intervals.

#### Primary analysis

The primary analyses will focus on establishing the predictive accuracy of the urine LAM assay compared to both NTM culture results from the day of sampling and aggregated culture results from within a year of the LAM measurement date. As a secondary endpoint, we will focus on how well a positive urine LAM assay predicts a positive NTM culture over a three year period. For the primary endpoints, the classification performance of the LAM assay will be assessed with respect to its ability to predict a positive culture at the time of the test and over the 12-month period prior or following the test. Of primary interest are the test’s sensitivity and specificity, but we will also investigate positive predictive power, negative predictive power, percent-agreement, and Cohen’s Kappa. These values will be computed twice using the binary results of the LAM assay (positive or not-positive) paired with either the binary culture results from the time of the test or with the aggregated results over the study interval (*i.e*. ≧1 positive culture versus no positive cultures). We will also investigate if the continuous abundance of LAM is a useful measure by calculating area under the receiver-operator curve, again using culture from the time of the test or aggregated over the 12-month period. Additionally, the multiple repeated observations for each individual in the two 12-month follow-up periods will allow us to perform a time-to-event analysis associating the LAM assay to culture results. Here, Cox proportional hazards regression models will be utilized with time to first positive NTM culture as the outcome and LAM assay (using both the continuous and binary versions) as the time-varying covariate of interest.

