## Figures and Tables

**Figure 1. F1:**
[figure not shown]
PAINLESS schedule of events. ^a^ Refer to PAINLESS Study Timeline (Figure 2). ^b^ On-study clinical follow-up visits will occur as clinically indicated in clinic, the hospital or at home. ^c^ End-of-study visit will be the first clinical visit occurring > 9 months after the start of Observational Year 2. ^d^ Study personnel will continue to review NTM culture results and clinical events recorded in the CFFPR for up to 5 years following end of study. ^e^ Samples may be obtained in clinic, the hospital or at home, either expectorated or sputum induction. If results from oropharyngeal swab or bronchoscopy are available, they will also be recorded. ^f^ Urine sample must be collected within 30 days of a sputum sample at the start of Year 1 and Year 2. End-of-study urine sample does not need to be linked to a sputum sample. ^g^ Standard clinical assessments will be obtained from CFF patient registry database. ^h^ Replacement urine for LAM assay if needed.

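### The primary LAM accuracy window includes the 12 months before the urine, although the objectives are forward prediction, and its length is described inconsistently

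*Protocol article*

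**What the plan says.** All references are to the protocol article.

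- **Objectives (Introduction).** The primary objective is whether LAM can foretell that cultures stay negative for a year. A secondary objective is to "predict a new positive NTM sputum culture within 12 months". Both run forward from the urine.
- **Classification window (Primary analysis).** LAM is judged on its ability to "predict a positive culture at the time of the test and over the 12-month period prior or following the test".
- **Other descriptions of the window in the same section.** The opening sentence has "aggregated culture results from within a year of the LAM measurement date", with no direction. The accuracy measures use "aggregated results over the study interval", with no length. The ROC analysis is described as "again using culture from the time of the test or aggregated over the 12-month period", again with no direction.
- **Number of analyses.** "These values will be computed twice using the binary results of the LAM assay (positive or not-positive"), once against the concurrent culture and once against the aggregate. Separate prior and following tables are not listed.
- **Urine schedule (Urine collection for LAM analysis).** Urine is collected at enrolment, at the start of Year 2 and at the end of study.
- **Length of the intervals.** Study Design gives 24±3 months in total. Figure 1, footnote c: "End-of-study visit will be the first clinical visit occurring > 9 months after the start of Observational Year 2".
- **Eligibility (Study population).** Participants have "at least one negative NTM culture within the year prior to enrollment and no known history of previous NTM positive cultures".

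**The concern.** Sensitivity against a culture that came before the urine measures detection of an infection already found. It does not measure prediction. The intended use in the Discussion is that a negative LAM spares further testing in someone without clinical suspicion, and only the forward window speaks to that.

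Look-back content also differs by urine. Before the enrolment urine there are no known positives, because eligibility excludes them. At the second and third urines, the look-back overlaps the follow-up of the preceding urine. A mixed estimate would therefore have no single clinical meaning. In addition, the article allows an extra urine after a positive culture is found; if that urine were analysed under this window, it would be a case by construction.

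The varying names for the window add a second problem. If the aggregate follows the actual observation interval, participants have unequal time in which to become a case.

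**Working it through.** **Inputs.** From the article: 100 participants and about 13 with a new positive culture over two years (Sample size); urines at nominal months 0, 12 and 24; total follow-up 24±3 months. Assumed here: only the first positive culture counts, and events are spread evenly, 6.5 per year.

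**The plan's own figure.** The 13 rests on centre data that are not shown, so it cannot be reproduced. It implies an annual risk of 1 − √(1 − 0.13) = 6.7%. The only other rate given, about 20% over five years in CF generally (Introduction), yields 100 × (1 − 0.8^(2/5)) = 8.5 over two years. The sources differ, so this neither confirms nor refutes the 13, and the point does not depend on it.

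**Step 1. Positive test windows on the nominal schedule, no post-study events.**

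| Urine | Look-back | Forward | Both pooled |
|---|---|---|---|
| 1 (month 0) | 0 | 6.5 | 6.5 |
| 2 (month 12) | 6.5 | 6.5 | 13 |
| 3 (month 24) | 6.5 | 0 | 6.5 |
| Total | 13 | 13 | 26 |

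**Step 2. Other schedules.** With pooled ±12-month windows, urines at 0/12/21 put 86% of on-study events in two windows and 14% in three (mean 2.14). Urines at 0/12/27 put 22% in one and 78% in two (mean 1.78). A forward-only window gives exactly one per event at 0/12/24 and 0/12/21. At 0/12/27 it misses 11%, those after month 24.

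**Step 3. Forward year of the third urine.** If the registry supplies it, at 6.7% per year among the 87 still negative it adds 87 × 0.067 ≈ 5.9 events (measured as new positives). Forward windows become 13 + 5.9 = 18.9 and pooled windows 18.9 + 13 = 31.9. The look-back share falls from 13/26 = 50% to 13/31.9 = 41%.

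**Step 4. Effect on sensitivity (assumed marker).** Suppose LAM turns positive only after culture conversion and then stays positive, so it predicts nothing. Forward sensitivity is 0/13 = 0%. Pooled sensitivity is 13/26 = 50%, or 13/31.9 = 41% with the Step 3 events.

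**Step 5. Effect on apparent precision (assumed 85% sensitivity).** Exact 95% intervals are 55–98% for 11/13 and 65–96% for 22/26. The second is falsely narrow if the 26 come from 13 people and are treated as independent.

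**Step 6. Effect of interval length.** With a 12-month Year 1, the stated ±3 months makes Year 2 between 9 and 15 months. At constant hazard, the risk is 1 − 0.87^(9/24) = 5.1% at 9 months, 6.7% at 12 and 1 − 0.87^(15/24) = 8.3% at 15. The ratio is 8.3/5.1 = 1.6.

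**The case against.** The strongest reply is that the article never says the two directions are pooled, or that the test rather than the participant is the unit. Prior or following could mean two separate assessments, and one status per participant per interval would count each event once. That stands as far as double counting goes: a reader might infer that every event counts twice, but the text does not establish it, and on permitted schedules the number of windows per event runs from one to three. It does not remove the defect, because the section names a backward window under prediction and lists only one aggregated analysis.

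Other stronger readings also go too far:

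- *The enrolment look-back contains no positives by design.* It contains no **known** positives. The paired sputum may precede the urine by up to 30 days and culture takes up to eight weeks, so a pending positive can fall there. Table 1 also restricts the exclusion to pathogenic NTM.
- *The interval has no upper limit.* This is true of footnote c alone, but Study Design gives 24±3 months.
- *Independence is assumed.* The article is silent on interval estimation, and that detail may sit in an analysis plan not shown.

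It can further be said that the planned Cox model, with LAM as a time-varying covariate, already looks forward and counts a first event once. That is correct, but it is an additional analysis and does not repair sensitivity and specificity, which the section names as of primary interest. Finally, culture is insensitive and often unavailable, so a wider reference window has a rationale. That supports reporting the look-back, but not inside a predictive endpoint. The study is also a single-centre pilot with no stated success threshold, which limits the consequences without changing what is estimated.

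**Conclusion.** The concern holds. As written, cultures that precede the urine can count toward the primary predictive accuracy, against the forward objectives, and the window is named in four non-equivalent ways within one section. This is a stated rule that yields the wrong quantity, not a detail left for later.

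The size is conditional. The 26 against 13 windows, and the 50% against 0% sensitivity, require per-test pooling of both directions, a 0/12/24-month schedule, and no events counted after the third urine; the sensitivity figures also require the assumed late marker. A reader might infer that the mix always inflates sensitivity, or that exactly half of the positives are not predictions. The documents support neither: if LAM clears after a transient infection the bias could run downward, and post-study events bring the look-back share to about 41%. In every case the pooled figure is not the predictive accuracy that the objectives ask for.

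**What to change.** 1. Define the primary aggregated endpoint as at least one positive NTM culture collected from the urine date to 12 months after it. Use the same length for every urine, and date cultures by collection, not by result. Use this definition wherever the section now has another description of the window.
2. Where the study interval ended early, and after the third urine, complete the 12 months from the medical record or the CFFPR.
3. Keep the paired culture as a separate concurrent analysis, and state which table a paired culture taken on or after the urine date enters.
4. Report any look-back association only in a separate table labelled exploratory.
5. State the unit of analysis. If repeated urines are pooled, use participant-level (cluster) intervals.

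**Cost.** This takes a short rewrite of the endpoint definition and some programming; registry review for up to five years is already planned. There will be fewer nominal positives and wider intervals. When a visit runs late, a few events fall between forward windows (11% on a 0/12/27-month schedule), though the Cox analysis of time to first positive culture can still use them.
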